### Potential Confounding and Influencing Factors

The meta-analysis carried out by Eijlers et al [11] indicates that VR-based distraction from anxiety and pain is more efficacious in younger children than in older children. Age and gender influence the perception of pain and anxiety during medical procedures. Younger children tend to report more pain during procedures such as venipuncture [16]. In self-reporting, girls tend to report more pain than boys [17]. However, older children and boys tend to rate pain and anxiety differently compared to younger children and girls [17]. Age and parental predictions of distress are substantial predictors of pain and anxiety on blood tests [18]. Therefore, age and gender will be considered as possible influencing factors in the analysis.

Our intervention addresses a range of medical procedures that have shown to be highly anxiety- and stress-inducing in pediatric patients but can generally be performed without anesthesia. It is possible that patient anxiety and pain ratings differ for different procedures and that these perceptions influence the effect of our intervention.

Fundamental anxiety as a patient characteristic (ie, trait anxiety) is also a likely influencing factor for anxiety and pain ratings [19]. Furthermore, there is evidence in the literature of a link between perceived anxiety and postoperative recall of pain [20], which could influence patients’ retrospective assessment of their pain. Therefore, we will consider the assessment of the caregivers and the observation of the interviewers in our study.

A well-documented phenomenon that negatively impacts the VR gaming experience is simulator sickness, which includes symptoms such as nausea, dizziness, headaches, and eye strain. There is evidence that children are less likely to react to VR exposure with these negative symptoms [21], but there have been few studies on the possible relationship between age and different forms of visually induced motion sickness. Nevertheless, we will record any indications of simulator sickness before and after the intervention as the described symptoms may relate to patients’ general health state. We have elaborated more on that topic in the Methods section, under the Simulator Sickness subsection.

Previous hospital experience, particularly about the previous interventions of the same or similar nature, as well as needle-related phobias and trauma, can influence the patient’s emotional response to the medical situation and will therefore be documented during screening. The actual diagnosis will also be recorded to assess the overall psychological situation of the patient and caregiver.

### Ethical Considerations

This study was approved by the ethics committee of the medical faculty of the University of Duisburg-Essen (22-10873-BO). The ethics committees of the other study centers, Universitätsklinikum Hamburg-Eppendorf, Germany, Ethik-Kommission der Ärztekammer Hamburg (approval 2023-200739-BO-bet) and Ethikkommission des Universitätsklinikum Schleswig-Holstein, Lübeck, Germany (approval 2023-708), also saw no ethical or legal objections to this study.

All patients and caregivers will be fully informed about the background and procedure of the study during the recruitment process before they consent to participate in the study. Both the legal guardians and the children must give their written consent to participate in the study. They will be informed about the protection of their personal data and their digital rights in accordance with the European General Data Protection Regulation.

During the onboarding process, the collected data will be pseudonymized. An individual, random participant ID will be created during enrollment and stored with the patient ID separate from the survey answers. Once data collection is complete, the pseudonymization table will be deleted so that the data are anonymous from this point on. The children will be informed of the possibility that they might undergo the procedure in the control group without HMD and sedation or anesthesia. Participants in the control group will be allowed to try the game after completing the medical procedure.

### Study Design

The study presented here is a prospective multicenter randomized nonblinded clinical trial. This study refers to protocol version 19 (March 1, 2023), which is registered in the German Clinical Trials Register (DRKS00033544). Any changes to the protocol will be submitted as an amendment to the responsible ethics committee of the University Hospital Essen for approval and filed in the DRKS. Data collection will take place at the University Hospital Essen, the University Hospital Schleswig-Holstein in Lübeck, and the University Hospital Hamburg-Eppendorf, all 3 located in Germany. Patients in the VR condition will play the game SDVR with 1 caregiver during the medical procedure. The beneficial effects of VR and digital games in distracting from anxiety and pain compared to the standard of care (ie, no intervention for distraction or sedation) have been demonstrated in numerous studies [9,11-13]. Therefore, our study particularly focuses on the effect of the shared gaming experience and addresses both the patient and the caregiver as recipients of the distraction and mood-enhancing intervention. Furthermore, to avoid the results being biased simply by the patient’s experience of getting an “extra treatment” and additional attention from the medical staff during participation in the study, we will compare the experimental condition with a control condition in which the patients and caregivers will also receive special treatment. Acoustic relaxation techniques are straightforward and unobtrusive to implement in medical procedures, making it possible to address both patients and caregivers simultaneously. In contrast to guided imagery, which requires active mental engagement—often challenging in stressful or painful situations—nature sounds offer a passive form of relaxation. This passivity makes them more accessible and appealing across a range of ages and cognitive abilities. Another option could be passive music therapy; however, natural sounds present a more universally neutral and calming experience, as they bypass personal musical preferences and the emotional resonance often associated with music. Therefore, we chose to play a recording of ocean waves to foster a calming atmosphere during the procedure.

### Procedure

A diagram of the study procedure is shown in Figure 1. Patients meeting the eligibility criteria (Textbox 2) will be identified in the hospital information system. Patients and their caregivers will then be contacted by telephone or during their next stay in the hospital. They will be fully informed about the background and aim of the study, the procedure, and the 2 experimental conditions. Patients and caregivers will then have at least 24 hours to consider whether they want to participate. Refusals and their reasons will be recorded anonymously.

If they agree to participate, patients and caregivers will be asked to give their written consent. During registration, the patients will then complete the screening questionnaire together with an interviewer, based on which the randomized, stratified group allocation will be automatically performed. All questionnaires aimed at patients will be completed together with the interviewers. The task of the interviewers is to read out the questions and items if necessary and to help with comprehension problems. The interviewers are trained accordingly so that they do not interfere with the patient’s response behavior and do not suggest answers.

The participants will be requested to arrive 60 minutes before the actual appointment. During this time, the patients and caregivers will fill out the preexamination questionnaires in parallel. The participants will be reminded once again that participation is voluntary and that they can withdraw their participation at any time.

**Figure 1 figure1:**
[figure not shown]
Study procedure timeline. Participants are assigned to either the experimental group (ie, Sweet Dive VR; SDVR) or the control group (ie, ocean waves). Pre- and postexamination questionnaires are administered to patients and caregivers. The interviewers assess the situation during the intervention using an observation protocol. CG: control group; EG: experimental group.

Participant inclusion and exclusion criteria.
**Inclusion criteria**
Age 6 to 12 years (applies for patients only)Procedure possible without sedation or anesthesia (applies for patients only)Sufficient knowledge of German (applies for patients and caregivers)Ability to hold and operate a game controller (applies for patients and caregivers)
**Exclusion criteria**
Visual impairments (eg, lack of stereo vision and color blindness; applies for patients only)Severe cognitive impairments (as assessed by the caregivers and physicians; applies for patients and caregivers)Diagnosed with epilepsy (applies for patients only)
**Termination criteria**
Desire to end participation (applies for patients and caregivers)Clear signs of severe simulator sickness (applies for patients only)Extreme pain (applies for patients only)Extreme anxiety (applies for patients only)Other adverse events (applies for patients and caregivers)

In the SDVR condition, patients and caregivers will receive a verbal, written, and illustrated explanation from the interviewer about the process, goal, and controls of the game as well as a brief introduction to the background story either as a short video or in the form of a short picture story. The caregivers will be instructed that they can start the game using the buttons on the controller and trigger events in the game that correspond to the treatment steps.

After the patients and caregivers have entered the examination room, in the SDVR group, the interviewer will help the patient put on the HMD and hand them the controller. The caregivers will receive the game controller and can then start the game session. In the control condition, the audio file will be played from a tablet or notebook.

We made special efforts to make the setup process as straightforward and quick as possible to enable noninvasive and seamless integration into the medical procedure. The VR app starts automatically as soon as the HMD is switched on (ie, the so-called “kiosk mode”). The necessary realignment of the perspective in the virtual world to the patient’s position can be triggered simply by pressing a button on the game controller. The technical setup process, including a functional test of all components (eg, Bluetooth connection to the game controller), takes just 5 minutes on average and can be prepared before the actual treatment. Setting up and adjusting the HMD for the patient and handing over the game controller to the caregiver takes a further 1 to 2 minutes on average.

During the procedure, the interviewer will observe the medical situation, the patient’s reactions, and the interaction between the patients and the caregivers. The observations will be documented in an observation protocol.

At the end of the intervention, the postexamination questionnaires will be completed by the patients and caregivers. Interruptions and premature terminations of the intervention will be recorded, and the reasons will be noted. Children in the control condition will be allowed to try out the game after the end of the experiment.

If a participant wishes to terminate the intervention or if one of the termination criteria described in Textbox 2 is met, the intervention will be discontinued immediately, and the participant will return to the standard of care, and a note will be made in the observation protocol.

### Participants

#### Sample

Patients requiring port puncture, lumbar puncture, peripheral or central venous catheter insertion, or Kirschner-wire removal will be enrolled, each with 1 caregiver. Given the complexity of the planned study setting and its integration into the clinical processes, we performed a sensitivity analysis to ensure an appropriate test strength and sample size. We anticipate that the recruitment of 78 patients and caregivers each is feasible. On the basis of a power analysis with the G*Power software [22] and starting from a 2-sided *t* test with a significance level of α=.05 and a test power of 80%, we determined that a medium-size effect of approximately Cohen *d*=0.64 can be achieved with a corresponding sample size of 39 participants per group. In view of these statistical parameters and considering the objectives of the study, we decided that recruiting 26 participants in each of the 3 participating study centers would provide an appropriate balance between practical feasibility and statistical power.

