## Results

Data collection is ongoing at the time of publication of this study. As of November 2024, we enrolled 39 patients and caregivers, 28 of whom completed the study (Multimedia Appendix 2 presents the participant flow diagram).

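### The stated 80% power at d of about 0.64 assumes that all 78 recruited children are analysable, because the recruitment target equals the calculated number with no allowance for loss

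*Protocol article*

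**What the plan says.** The Sample section of the protocol article works from feasibility to a detectable effect. It begins with the recruitment the team expects: "We anticipate that the recruitment of 78 patients and caregivers each is feasible". Using G*Power and "starting from a 2-sided *t* test with a significance level of α=.05" with 80% power, it finds that "a medium-size effect of approximately Cohen *d*=0.64" "can be achieved with a corresponding sample size of 39 participants per group". It then fixes the target: "we decided that recruiting 26 participants in each of the 3 participating study centers", that is, 3 × 26 = 78.

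Other sections bear on how many of the 78 will have outcome data:

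- The termination criteria (Textbox 2, under Procedure) include a wish to stop, severe simulator sickness, extreme pain, extreme anxiety and other adverse events. The intervention is then discontinued.
- The Challenges section expects that some children may want to take the headset off during the procedure.
- The Results section reports that by November 2024 "we enrolled 39 patients and caregivers, 28 of whom completed the study". It says that data collection is ongoing and refers to a participant flow diagram in Multimedia Appendix 2, which is not part of the text at hand.

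**The concern.** A sensitivity analysis gives the effect that can be detected with the number of participants **analysed**. Here the number entered is the number **recruited**. The two agree only if every recruited child contributes to the comparison, and the article's own termination criteria and interim count make that an optimistic premise.

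The point matters most for the child's self-reported pain, which belongs to the primary hypothesis. Table 1 lists the child's pain scale only at the post-intervention measurement, so a child who does not reach that questionnaire has no self-rated pain value.

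At stake is how the result is read. If the comparison is not significant, readers will take the trial to have had 80% power for d of about 0.64. With any loss, the true figure is lower and the smallest effect detectable at 80% power is larger.

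**Working it through.** **Inputs from the article.** Two-sided two-sample t test, α=.05, 80% power, d≈0.64, 39 per group (Sample). Recruitment 3 × 26 = 78 (Sample). Interim completion 28 of 39 (Results).

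**Assumption.** The article gives no loss rate, so a range is used. Loss is split equally between the groups.

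**Formula.** With n analysed per group, df = 2n − 2, noncentrality λ = d·√(n/2), and critical value t\* = t(0.975, df). Power = P(|T| > t\*), where T follows a noncentral t distribution with df and λ. The detectable d is the value at which power equals 80%.

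**Step 1: reproduce the stated figure.** For n = 39, df = 76, t\* = 1.992 and λ = 0.64 × √19.5 = 2.826. Power is 79.7%, and the detectable d is 0.643. The article's 0.64 is reproduced, so the arithmetic is correct.

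**Step 2: compare recruited with analysed.** The calculation uses 2 × 39 = 78 and the recruitment target is 3 × 26 = 78. The implied loss is 78 − 78 = 0.

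**Step 3: the interim count.** 28/39 = 71.8% completed, and 11/39 = 28.2% had not completed at that date. Applied to 78, this gives 78 × 28/39 = 56, or 28 per group.

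**Step 4: recompute over a range of loss.**

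| Assumed loss | Analysed per group | Power at d=0.64 | Detectable d at 80% power |
|---|---|---|---|
| 0% | 39 | 79.7% | 0.64 |
| 5% (78 × 0.95 = 74.1) | 37 | 77.5% | 0.66 |
| 10% (78 × 0.90 = 70.2) | 35 | 75.2% | 0.68 |
| 15% (78 × 0.85 = 66.3) | 33 | 72.6% | 0.70 |
| 28.2% (11/39, if it persisted) | 28 | 65.2% | 0.76 |

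The last row is conditional. The exact 95% confidence interval for 28/39 runs from 55% to 85%. Even if the count were a final completion rate, power at d=0.64 could lie anywhere from about 54% to 73%.

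**Step 5: the label.** By the usual convention a medium effect is d=0.5 and a large one is 0.8. At d=0.5 with all 39 per group analysed, power is 58.7%.

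**The case against.** The strongest case on the other side has five parts.

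- **The calculation is right.** This stands. The issue is which number was entered, not how the formula was worked.
- **28 of 39 is not a dropout rate.** This also stands. Data collection is ongoing, and under Procedure the consent, screening and allocation come before the appointment, so some of the 11 may simply be waiting. A reader might infer from the interim count that 28% will be lost and that the design therefore fails to deliver its stated power. The article does not support that. It does not say what happened to the 11, and the flow diagram that may show it is in an appendix not at hand. For the same reason, no complaint can be made that the split into pending and lost is missing.
- **Not completing is not the same as not analysable.** This stands in part. Several hypotheses rest on observer or caregiver ratings, which a child who stops early may still have. So 28 per group is one conditional case and not a forecast.
- **The label medium-size sits beside the exact d.** This stands. A reader might infer a claim of 80% power for d=0.5, but the article makes no such claim. The label is at most loosely chosen.
- **The full protocol or analysis plan may deal with attrition.** This does not remove the point. The article states a recruitment target equal to the number its calculation needs, which leaves no room for an allowance.

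**Conclusion.** The point holds as a qualification of the stated power. The figure of 80% at d of about 0.64 is correct for 78 analysable children and for no smaller number, yet 78 is also the recruitment target. Any loss makes it too favourable. The shortfall is modest at small losses: about 2 percentage points of power at 5% loss, 5 at 10% and 7 at 15%. It reaches about 15 points only if the interim share of 28/39 persisted and no non-completer were analysable.

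The losses of 5% to 15% are assumptions, because the article gives no rate. The calculation also assumes equal loss in the two groups and the two-sample t test that the article names. Severity is moderate: the sample size, conduct and analysis are unaffected, but the precision of the trial is described more favourably than its recruitment target supports.

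**What to change.** Restate the sensitivity statement in the Sample section for the number analysable, over a range of assumed loss. For example:

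> An effect of d=0.64 is detectable with 80% power only if all 78 children are analysable. With about 10% loss (35 per group), the detectable effect is d=0.68 and power at d=0.64 is 75%. With 15% loss (33 per group), the figures are 0.70 and 73%. If the interim completion share of 28/39 persisted (28 per group), they would be 0.76 and 65%.

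Optionally, drop the label medium-size and leave the numerical d, since power at d=0.5 is 59% even with full retention.

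The cost is wording only. No extra recruitment is asked for and the design does not change. The stated figure becomes slightly less favourable, and the change can be made while data collection continues.

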#### Randomization and Stratification

Assignment to the experimental conditions will be automated by a study management software. The recruiters will have no opportunity to influence the assignment at any time. Allocation will use the method of stratified randomization using a minimization algorithm. Consequently, the patient-related variables (ie, strata) used for sample stratification, are as follows: (1) trait anxiety (State-Trait Anxiety Inventory for Children–trait anxiety), (2) age, (3) type of intervention, (4) previous experience with the procedure, and (5) sex. The minimization algorithm attempts to allocate a new patient to a group in such a way that the difference between the 2 groups is minimal for each stratum. If no clear allocation can be achieved with this procedure, a random allocation will be made.

### Material

#### Experimental Condition: SDVR

The players’ mission will be to catch as many fish as possible for a medical examination after a cargo ship lost a container filled with candy. The patient and 1 caregiver will play the game cooperatively. The core mechanic of SDVR is attracting and catching fish. To attract a fish, the patient can drop a piece of candy into the water by pressing a button. A transport box moves horizontally on the upper edge of the screen from left to right and back. When the box is precisely above the fish, the patient must press another button at the right moment to bring it down and cover the fish. In the next step, the patient must inform the caregiver verbally so that the caregiver can press a button on the gamepad to move the box upward. The fish is then considered to be collected, and the process can start all over again. The number of fish collected will be shown to the VR player in a head-up display (Figure 2). The gameplay is infinite; that is, there is no fixed game end or goal. This way, we can respect the variable length of the treatment.

**Figure 2 figure2:**
[figure not shown]
In “Sweet Dive VR,” the patient must attract a fish with candy and move the box down in the right moment to collect it. Next, the caregiver must move the box up again. The head-up display in the upper-left corner indicates the number of collected fish (top row) and events associated with the medical procedure triggered by the caregiver (bottom row).

The game was designed to be played in a supine position (Figure 3). Consequently, the player’s perspective has been adjusted so that, while lying on their back, they not only look up at the virtual sky (ie, the virtual water surface as in the case of SDVR) but can also see the horizon and the ground. By slightly shifting the virtual camera, a natural visual impression is possible, suggesting that the player is standing. In numerous previous tests, we have not registered any negative effects such as simulator sickness.

The key feature of our game design is the inclusion of a caregiver in the gameplay as a second player. Through the asymmetrical game design [23], we can distract both the patient and caregiver from the treatment and create a shared positive experience. While both players must cooperate to pursue their shared objective (ie, catching the fish), they have different mechanics at their disposal to achieve that objective. However, not only are the actions available to the 2 players different but also the information about the game world is different. While the patient can see the game world via the HMD, the caregiver lacks all visual and auditory cues about the current game state (Figure 3). Thus, the caregiver is completely dependent on the communication of their child. Consequently, a high degree of concentration on the game events and the verbal communication of both players is required, which thus becomes an essential mechanic of the game and enhances the immersion of both players [14]. With the children giving verbal instructions to their caregivers, the game is designed to support their feeling of being in control over the situation. Moreover, the strong focus on communication between caregivers and children should enhance the sense of familiarity, security, and connectedness within the emotionally challenging situation. In addition to interacting with the child through the game, caregivers are assigned the task of responding to specific steps of the medical procedure (eg, the application of a disinfectant or an oxygen cannula) by triggering corresponding in-game events. This approach synchronizes the virtual world with the patient’s real-world sensory experiences, thereby preserving and enhancing the patient’s immersion. Concurrently, it grants caregivers a sense of agency and participation in the medical situation, reinforcing their involvement in the process.

As this study focuses on the description of the research protocol for the clinical evaluation of our approach, we refrain from delving deeper into the design rationale here and refer to the planned publication elsewhere.

